**Methods/Design:**

A single-centre, prospective, randomised, double-blind, placebo-controlled trial of 120 subjects with stage 3 chronic kidney disease recruited from University Hospitals Birmingham NHS Foundation Trust. Baseline investigations include transthoracic echocardiography and cardiac magnetic resonance imaging to assess ventricular mass, volumes and function, applanation tonometry to determine pulse wave velocity and pulse wave analysis as surrogate measures of arterial stiffness and dual energy x-ray absorptiometry scanning to determine bone density. During an open-label run in phase, subjects will receive 1600 mg sevelamer carbonate with meals for four weeks. They will then be randomised to either continue sevelamer carbonate or receive an identical placebo (60 subjects per arm) for the remaining 36 weeks. Four-weekly monitoring of serum electrolytes and bone biochemistry will be performed. All baseline investigations will be repeated at the end of the treatment period. The primary endpoint of the study is a reduction in left ventricular mass after 40 weeks of treatment. Secondary endpoints are: i) change in aortic compliance; ii) change in arterial stiffness; iii) change in arterial elastance; iv) change in left ventricular systolic and diastolic elastance; v) change in left ventricular function; and vi) change in bone density.

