**Figure 1 F1:**
[figure not shown]
**Study timeline**. 120 subjects will undergo baseline investigations before entering a 4 week open-label run-in phase in which all subjects will receive 1600 mg of sevelamer carbonate with meals. Participants will then be randomised to continue treatment with sevelamer carbonate 1600 mg with meals or identical placebo for the remaining 36 weeks. Safety monitoring will be performed every four weeks. Investigations will be repeated at week 40 after which subjects will have completed participation in the study.

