### Subject Withdrawal

Withdrawal criteria are listed in Table 4. The average serum phosphate level of patients with stage 3 CKD enrolled in a previous study by the investigators was 1.2 ± 0.2 mmol/L [38]. It is therefore felt unlikely that significant numbers of participants will need to be withdrawn because of hypophosphataemia. The majority of patients with stage 3 CKD do not require phosphate-binding medication for overt hyperphosphataemia and the prevention of metabolic bone disease. Should any subjects in the placebo group develop serum phosphate >1.8 mmol/L, they will be withdrawn from the study and rescue therapy with appropriate phosphate binders will be administered.

**Table 4 T4:** Withdrawal criteria

Withdrawal Criteria
Pregnancy
Hypophosphataemia (serum PO_4 _<0.8 mmol/L despite dose reduction of treatment/placebo)
Hyperphosphataemia (serum PO_4 _>1.8 mmol/L in subjects receiving placebo)
Occurrence of any serious adverse event, intercurrent illness or laboratory abnormality which, in the opinion of the investigators, warrants the subject's permanent withdrawal from the study
Poor compliance with study medication
Poor attendance at study visits
Subject inability to tolerate study medication due to side effect profile
Subject decision to withdraw
Deteriorating renal function
Subject lost to follow-up (loss of contact before final study visit)

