### Planned Statistical Analysis

Comparisons will be performed between the groups at baseline and after the 36-week treatment phase. The normality of distribution of all continuous variables will be determined using a normality plot and the Kolmogorov-Smirnov test. Normally distributed variables will be analysed using unpaired t-tests, χ^2 ^or repeated measures analysis of variance with corrections made for multiple comparisons. Variables not normally distributed will be log transformed prior to analysis to achieve normal distribution or, if this is not achieved, analysed by Mann-Whitney U or Kruskal-Wallis tests. Multiple linear regression models will be derived for left ventricular mass and measures of vascular and cardiac stiffness using stepwise regression analysis. Analysis will be by intention-to-treat. A p-value of <0.05 will be considered statistically significant.

Sample size calculations were based on the primary endpoint of change in left ventricular mass after 40 weeks of treatment. A previous study by our group evaluating the cardiovascular effects of spironolactone in patients with early CKD revealed a 14 g drop in left ventricular mass from baseline following 40 weeks of therapy [38]. Using data from this previous study, 55 subjects in each arm will provide at least 80% power of detecting an 8 g difference between the change in left ventricular mass from baseline to 40 weeks using a two-tailed t-test at the 5% significance level given a standard deviation of 15 g in the change in left ventricular mass from baseline. Recruiting 60 subjects to each group will allow a 10% withdrawal or dropout rate.

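### The same 120 subjects are counted at entry to the run-in and as 60 randomised per arm, although withdrawal between those points is planned

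*Protocol article*

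**What the plan says.** Three places in the protocol article give the trial's size.

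- The Figure 1 legend counts before the run-in: "120 subjects will undergo baseline investigations before entering a 4 week open-label run-in phase".
- The abstract (Methods/Design) counts after it: "They will then be randomised to either continue sevelamer carbonate or receive an identical placebo (60 subjects per arm".
- Planned Statistical Analysis states that "55 subjects in each arm will provide at least 80% power" for an 8 g difference in change in left ventricular mass with an SD of 15 g, "using a two-tailed t-test at the 5% significance level", and then: "Recruiting 60 subjects to each group will allow a 10% withdrawal or dropout rate".

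The Run-in Phase section gives four weeks of open-label sevelamer to everyone, to look at tolerability, compliance and side effects among other things. Table 2 there provides for withdrawal at week 4 or week 6, before randomisation, when serum phosphate stays low. The document states no expected run-in loss. On low phosphate, Subject Withdrawal gives a judgement without a rate: "It is therefore felt unlikely that significant numbers of participants will need to be withdrawn because of hypophosphataemia".

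**The concern.** If 120 people enter the run-in and 60 per arm are randomised at its end, nobody can have left in between. Yet the plan itself sets out a route for leaving at that stage. One of the two counts must therefore be wrong, or at least is not what is meant.

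The difference matters because run-in losses are not ordinary dropout. A subject who leaves before allocation belongs to neither arm. Intention-to-treat analysis cannot bring that subject back, and neither can the final measurements taken at withdrawal. If 120 is the entry number, every run-in loss reduces the randomised number on which the power statement rests. The text also does not say whether the single 10% allowance starts at entry or at randomisation.

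**Working it through.** **Inputs.** From Planned Statistical Analysis: difference 8 g, SD of change 15 g, two-sided 5% t-test, 55 evaluable per arm, 60 recruited per arm, 10% allowance. From the Figure 1 legend: 120 at entry. The run-in loss is not given, so 5%, 10% and 20% are assumed below to show a range.

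**Step 1: the plan's own figure.** By the normal approximation, n per arm = 2 × (1.960 + 0.842)² × (15/8)² ≈ 55.2, which rounds up to 56. Power at 55 is 79.9%.

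For the t-test that the plan names, power comes from the noncentral t distribution with 2n − 2 degrees of freedom and noncentrality 8 / (15 × √(2/n)). At n = 55 the noncentrality is 2.80 and power is 79.2%. At 56 it is 79.9% and at 57 it is 80.6%, so 57 per arm is the smallest number that reaches 80%. The plan's figure is reproduced to within a point, but it falls just short of 80% as stated.

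**Step 2: the 10% allowance.** 60 × 0.90 = 54, and power at 54 is 78.4% (79.1% by the normal approximation). Going from 60 to 55 is a loss of 5/60 = 8.3%. Keeping 55 after a 10% loss needs 55/0.9 = 61.1, so 62 per arm.

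**Step 3: the two counts.** If 120 enter and a fraction r leaves in the run-in, 120(1 − r)/2 are randomised per arm. This equals 60 only when r = 0.

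**Step 4: illustration if 120 is the entry number.** With a further 10% lost after randomisation, the number analysed per arm is 60 × (1 − r) × 0.9. Power is by the t-test, with fractional n carried through.

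| Assumed run-in loss | Randomised per arm | Analysed per arm | Power for 8 g |
|---|---|---|---|
| 0% | 60 | 54 | 78.4% |
| 5% | 57 | 51.3 | 76.3% |
| 10% | 54 | 48.6 | 74.0% |
| 20% | 48 | 43.2 | 68.8% |

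If instead the 10% covers every loss from entry to week 40, 120 × 0.9 / 2 = 54 per arm are analysed and power is again 78.4%.

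**The case against.** The strongest reply is that the sample-size text and the abstract agree. Groups exist only after allocation, so 60 per group means 60 randomised, and only a condensed figure legend says otherwise. Whether run-in failures are replaced is the kind of detail that an article leaves to the full protocol. The second part stands: the absence of a replacement rule is not a finding here. The first part makes it plausible that 120 randomised was intended. It does not remove the conflict, because the article itself prints both counts and they cannot both be true once anyone leaves in the run-in.

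A second reply is that the shortfall is speculative. It is right that the lower power figures depend on run-in losses the document never states. They also add those losses to a full further 10%, although a run-in that looks at tolerability and compliance might reduce later dropout. Some withdrawn randomised subjects have final measurements (Table 3) and might still contribute data. The table above is therefore an illustration and not a forecast.

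A reader might also infer that many subjects will be lost to low phosphate, because the reassurance in Subject Withdrawal rests on an earlier study's distribution (1.2 ± 0.2 mmol/L) while everyone here receives a binder. The document does not support a number for this. Phosphate below 0.8 mmol/L is an exclusion criterion, so the entry distribution is cut off there. Withdrawal also requires the low value to persist after dose reduction, and no on-treatment rate is given. No such claim is made here.

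**Conclusion.** The plan is wrong as written on one point: 120 cannot be both the number entering the run-in and the number randomised, unless run-in loss is zero. This follows from the text alone and needs no assumption.

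The size of the consequence is not fixed by the document. Power for 8 g is 78% if 120 are randomised and 10% are lost, or if the 10% covers all losses from entry. It is about 76%, 74% or 69% if 120 enter, 5%, 10% or 20% leave in the run-in, and 10% more are lost later. All these figures take the planned SD of 15 g and the stated t-test as given.

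Two stronger readings are tempting and do not hold. One is that the claim of at least 80% fails because 60 less 10% is 54 and not 55. That slip costs about 0.8 points (79.2% to 78.4%), and 55 per arm already misses 80% slightly, so it is a rounding matter and not the cause. The other is that the trial is shown to be materially underpowered. That would need a run-in loss rate, and the document gives none.

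**What to change.** State whether 120 is the number entering the run-in or the number randomised, and make the Figure 1 legend, the abstract and Planned Statistical Analysis agree. Say whether the 10% allowance runs from entry or from randomisation.

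If 120 is the number randomised, correct the legend so that it does not give 120 as the entry number. If 120 is the number entering, give the expected run-in loss and restate power at the number expected to be randomised and analysed. For example, power for 8 g would be about 74% if 10% leave in the run-in and 10% later.

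In either case, replace the claim of at least 80% by the t-test figure: 79% at 55 per arm, or 78% at the 54 that remain from 60 after 10% loss.

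The cost is wording and a slightly less favourable stated power. The restatement itself needs no extra subjects.

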### Monitoring and Safety Assessments

All adverse events, including serious adverse events (SAEs), will be recorded and followed up for the duration of the study or until resolution. Assessment of adverse events will be performed by the study investigators. All SAEs will be graded and reported to the sponsor. Any suspected unexpected serious adverse reactions will be reported to the sponsor, ethics committee and Medicines and Healthcare products Regulatory Agency. This study has been reviewed and approved by West Midlands Research Ethics Committee. Written informed consent will be obtained from all study participants.

## Summary

The demonstration of an important pathophysiological role for serum phosphate in the development of cardiovascular disease associated with CKD would be crucial in the understanding of this condition and have important implications for treatment. As left ventricular mass and arterial stiffness are prognostically significant markers in CKD, a positive effect would suggest that phosphate lowering in stage 3 CKD with the non-calcium-based phosphate binder sevelamer, in addition to conventional treatment for blood pressure and hypercholesterolaemia, is of prognostic value and would provide a rationale for a large clinical trial with cardiovascular morbidity and mortality as end-points.

## Abbreviations

Aix: augmentation index; AIx_75_: augmentation index corrected to a heart rate of 75 beats/minute; CKD: chronic kidney disease; CMR: cardiac magnetic resonance; DEXA: dual energy x-ray absorptiometry; ECG: electrocardiogram; ESKD: end stage kidney disease; GFR: glomerular filtration rate; PTH: parathyroid hormone; SAEs: serious adverse events
